**1. Adverse drug reaction in the digestive system**
Upset stomach
Loss of appetite
Nausea
Diarrhea
**2. Adverse drug reaction in the cardiovascular system**
Palpitation
Hypertension
Hypotension
Tachycardia
**3. Adverse drug reaction in the immune system**
Allergic reactions (rashes, pruritus and hyperhidrosis)
Anaphylactic shock
**4. Adverse drug reaction in the nervous system**
Activation insomnia
Dizziness

**Table 4 T4:** Termination criteria of CPET.

**1. Symptoms or signs of poor breathing and circulation**
Pale face, clammy skin
Cyanosis
Dizziness
Chest pain
Nausea
Severe difficulty breathing
Precardiac pain with ischemic ST changes greater than 2 mm
Severe hypertension (240/140 mmHg)
Systolic blood pressure drop >10 mmHg
**2. Occurrence of severe fatigue or severe leg pain, preventing the participants from pedaling**
**3. Failure of instrument**
More than three electrocardiogram patches fall off
An unexpected power failure
Bluetooth device disconnected
**4. Participant requests for reasons other than above**

### Outcomes

2.5.

The primary outcome will be the cardiorespiratory fitness characteristics both at high-altitude acclimatization and de-acclimatization after ubiquinol supplementation. Specifically, the parameters including peak oxygen consumption (VO_2_), % predicted peak VO_2_, VO_2_ at the anaerobic threshold (AT), peak O_2_ pulse, metabolic equivalents, % maximum predicted heart rate, rate pressure product, VE/VCO_2_ slope, oxygen uptake efficiency slope, VO_2_/work rate slope, cardiac output, exercise ventilatory power, circulatory power, and dead space ventilation / tidal volume at these four visits will be collected for further analysis. A brief definition of these indicators is as follows: peak VO_2_, peak oxygen consumption during an incremental exercise protocol with or without a plateau; % predicted peak VO_2_, peak VO_2_ divided by predicted peak VO_2_; VO_2_ at AT, the value of VO_2_ at AT time; peak O_2_ pulse, the peak oxygen extracted with each beat of the heart; metabolic equivalents, the ratio of exercise metabolic rate to resting metabolic rate calculated as VO_2_/3.5 ml/min/kg; % maximum predicted heart rate, heart rate divided by maximum predicted heart rate; rate pressure product, the product of heart rate and systolic blood pressure; VE/VCO_2_ slope, from exercise onset to peak exercise by the slope of linear regression of VE and VCO_2_; oxygen uptake efficiency slope, slope of the regression line of VO_2_ vs. log_10_ VE; VO_2_/work rate slope, *Δ*VO_2_/*Δ*work rate during incremental exercise; cardiac output, the amount of blood the heart pumps per minute; exercise ventilatory power, the ratio between peak SBP and the VE/VCO_2_ slope; circulatory power, the product of CO and mean arterial BP; dead space ventilation / tidal volume, an estimate of the ventilation-perfusion ratio. In addition, the detailed definitions and calculation methods of these indicators are shown in Table 5.

**Table 5 T5:** The measurement approach for each CPET variable.

CPET fitness measure	Physiological significance	Measurement methodology
Peak oxygen consumption (VO_2_)	“Gold standard” assessment of cardiorespiratory fitness.	The VO_2_ value of plateau attained when there is no further (or relatively small) increases in VO_2_ despite further increases in work rate is determined as VO_2_max (28). Consequently, peak VO_2_ is often used as an estimate for VO_2_max. For practical purposes, VO_2_max and peak VO_2_ are used interchangeably. Symptom limitation during an incremental exercise protocol could be taken to reflect the maximal VO_2_ value even though a plateau in VO_2_ fails to appear (29).
% predicted peak VO_2_	Comparison of peak VO_2_ achieved with predicted value for age, sex, and body size.	Using the Wasserman and Hansen formula (30).
VO_2_ at the anaerobic threshold (AT)	Anaerobic threshold refers to the critical point at which muscle metabolism transitions from aerobic to anaerobic metabolism in an incremental exercise test.	Measurement of VO_2_ and VCO_2_, with AT estimated as the breakpoint in the VCO_2_-VO_2_ relationship using the V-slope method (31).
Peak O_2_ pulse	Reflects stroke volume and peripheral O_2_ extraction. Indicates the peak capacity for oxygen extraction on each heart beat.	Peak VO_2_/peak heart rate.
Metabolic equivalents (METS)	The ratio of exercise metabolic rate to resting metabolic rate. Expresses the relative energy metabolism level of various activities based on energy consumption in quiet and sitting positions (32). 1 Met is defined as the consumption of 3.5 ml of oxygen per kilogram of body weight per minute (33).	VO_2_/3.5 ml/min/kg.
% maximum predicted heart rate	Heart rate response to exercise.	Peak heart rate as a percentage of the predicted peak heart rate calculated using the Tanaka formula (peak heart rate = 208–0.7*age) (34).
Rate pressure product (RPP)	Represents the relative level of myocardial oxygen consumption.	The product of heart rate and systolic blood pressure.
VE/VCO_2_ slope	Determined by the dead space fraction of the breath (VD/VT) and arterial PCO_2_. Typically taken to reflect the degree of match between alveolar ventilation and pulmonary perfusion.	Slope of the regression line of VE vs. VCO_2_ (35).
Oxygen uptake efficiency slope (OUES)	Reflects VO_2_ kinetics.	Slope of the regression line of VO_2_ vs. log_10_ VE (35).
VO_2_/work rate slope	Reflects the metabolic cost of performing external work.	Slope of the regression line of VO_2_ vs. work rate.
Cardiac output (CO)	Measures the strength of cardiac ejection	Using the equilibrium CO_2_ re-breathing technique of Collier (36).
Exercise ventilatory power (EVP)	An integrated index to predict risk representing synergistically linked assessment of ventilatory efficiency and hemodynamics, peak SBP reflecting systemic hemodynamics (37), and VE/VCO_2_ slope reflecting the complex interplay of peripheral and pulmonary abnormalities.	The ratio between peak SBP and the VE/VCO_2_ slope (38).
Circulatory Power (CP)	An index of cardiac systolic function (39).	The product of CO and mean arterial BP (40).
Dead space volume/tidal volume (VD/VT)	An estimate of the ventilation-perfusion ratio representing the efficiency of alveolar ventilation and blood flow matching. The physiological dead space is normally one-third of the tidal volume at rest (36).	[(PaCO_2_ − PECO_2_)/PaCO_2_] − (VDapp/tidal volume) where PaCO_2_ is the arterial CO_2_ pressure, PECO_2_ is the partial pressure of CO_2_ in mixed expired air, and VDapp is the apparatus dead space. PaCO_2_ can be estimated noninvasively using PETCO_2_ (41).

The secondary outcomes will be the questionnaire results of AMS and HADAS. The symptoms of these two diseases are shown in a later section. The effects of altitude and ubiquinol on them will be analyzed in detail in this study. Participants with severe disease symptoms, especially hypoxia-related symptoms, will receive additional treatment.

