### Setting

2.1.

This is a single-center, randomized, double-blind, placebo-control clinical trial conducted at Chongqing Xinqiao Hospital and Shigatse Branch Hospital [The Shigatse CARdiorespiratory Fitness (SCARF) Study] in 2022 and registered at www.chictr.org.cn (ChiCTR2200059900 and ChiCTR2200066328). The primary hypothesis of this study is that ubiquinol supplementation may improve cardiorespiratory fitness both at high-altitude acclimatization and de-acclimatization, while AMS and HADAS are secondary endpoints. The study complies with the SPIRIT 2013 recommendations (Standard Protocol Items: Recommendations for International Trials) (24) (Supplementary Material S1). Table 1 depicts the overall schedule and time commitment for trial participants.

**Table 1 T1:** Study schedule and time commitment.

Timepoint	Study period					
	Enrolment	Allocation	Post-allocation			Close-out
	−14 days	0	11 days	17 days	28 days	6 months
Enrolment						
Eligibility screen	X					
Informed consent	X					
Medical and travel history	X					
Vital signs	X					
Allocation/randomization		X				
Interventions						
Ubiquinol group						
Placebo group						
Assessments						
Baseline variables: age, sex, height, weight			X			
Outcome variables						
CPET			X	X	X	X
Blood routine examination			X	X	X	
Serum marker examination			X	X	X	
The Lake Louise 2018 score assessment				X		
High altitude de-acclimatization syndrome assessment					X	X

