#### Randomization, blinding, study treatment, and follow-up of participants

2.4.1.

Eligible subjects are randomized 1:1 into the ubiquinol group or placebo group by two physicians through a random code generator software (www.randomization.com) to receive either ubiquinol or placebo orally. These two physicians will solely operate randomization and drug distribution, and the randomization information will not be exposed to any participants or researchers, including laboratory staff, data gatherers, and statistical analysts throughout the study. Treatment allocation will be concealed in an opaque envelope opened on the day of treatment. Allocation will not be exposed until the end of the statistical data analysis or when any adverse event, such as severe diarrhea, occurs. A daily reminder email will be set up and sent to participants, and the rest of the medication will be sent back to us to assist in improving compliance. In addition, three serological tests of ubiquinol blood concentration can help monitor whether the participant is consistently taking the medication. The blinding will be maintained throughout the study. Clinical follow-up will be scheduled on days 11, 17, 28, and 6 months after the study began by performing cardiorespiratory tests or filling out self-administered questionnaires for symptoms. The primary outcome is cardiorespiratory fitness, while AMS and HADAS are the secondary endpoints. Safety endpoints include any reported adverse events (Table 3), exercise-limiting symptoms and pre-specified termination criteria (Table 4), and abnormal blood analysis results. The participants will have direct access to receive first aid from their treating team. Any adverse clinical event will be reported to the ethics committee.

**Table 3 T3:** Reported adverse events of ubiquinol (27).

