#### Statistical considerations

2.11.2.

Continuous variables will be expressed as means ± standard deviations (SD) or as median (interquartile spacing), and categorical variables as *n* (%) according to the Shapiro–Wilk test. Generalized estimating equations (GEE) with an exchangeable working correlation will be employed. Treatment, altitude, and the treatment multiplied by altitude interaction will be considered independent variables under mixed models. At each altitude, a comparative analysis will be carried out between two groups (ubiquinol group and placebo group), and the least significant difference method will be performed to adjust within-altitude differences for multiple comparisons. Correlation analyses will be performed using Pearson correlation for continuous variables, and Spearman Rank tests will be used between categorical variables. In addition, subgroups will be defined by age for analysis since it is known that ubiquinol levels decrease with age (23). Two-sided tests with *p*-values less than 0.05 will be considered statistically significant. IBM SPSS Statistics software for Windows (version 26, IBM, Armonk, NY, United States) will be used for statistical analyses.

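### The primary outcome is 14 exercise-test parameters at four visits, with no single primary variable, no success rule and no effective multiplicity control, so the false-positive rate of the main claim is uncontrolled

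*Protocol article*

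**What the plan says.** Under Setting (2.1), the primary hypothesis is that "ubiquinol supplementation may improve cardiorespiratory fitness both at high-altitude acclimatization and de-acclimatization". Outcomes (2.5) defines the primary outcome in the same broad terms: "The primary outcome will be the cardiorespiratory fitness characteristics both at high-altitude acclimatization and de-acclimatization after ubiquinol supplementation". It then lists the parameters, from peak VO2 to "exercise ventilatory power, circulatory power, and dead space ventilation / tidal volume at these four visits will be collected for further analysis". The list has 14 entries. The visits are set in section 2.4.1: "Clinical follow-up will be scheduled on days 11, 17, 28, and 6 months after the study began". Table 1 marks CPET at all four.

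Statistical considerations (2.11.2) puts treatment, altitude and their interaction in the model and adds: "At each altitude, a comparative analysis will be carried out between two groups". LSD is named as the adjustment for multiple comparisons within an altitude. On the threshold, two-sided p-"values less than 0.05 will be considered statistically significant".

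Table 5 and the Discussion call peak VO2 or VO2max the gold standard measure of cardiorespiratory fitness, but no section makes it the primary variable. Sample size (2.3) uses a single alpha of 0.05 and power of 0.9 and names no outcome.

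**The concern.** A 5% error rate belongs to one pre-stated test. Here the claim that ubiquinol improves cardiorespiratory fitness could rest on any of 14 parameters at more than one visit, each judged at 0.05. Nothing says which result decides, how many must agree, or what happens if they conflict.

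This is more than a detail left to an analysis plan, because the article does fix a multiplicity method and that method does not work. With two groups at an altitude there is one pairwise comparison, and LSD is then the unadjusted test. It does nothing across parameters.

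The list also counts overlapping quantities separately. By Table 5's formulas, metabolic equivalents are VO2 per kg divided by 3.5, O2 pulse is peak VO2 over peak heart rate, exercise ventilatory power contains the VE/VCO2 slope, and circulatory power contains cardiac output. One chance deviation can look like several agreeing findings.

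At stake is whether a reported primary result can be told apart from chance.

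**Working it through.** **The plan's own figure.** The plan gives no error rate for the set of primary parameters. Its only related figures are alpha 0.05 and the sample size: 39 × 1.05 = 40.95, rounded to 41. Neither is tied to a named parameter.

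**Inputs from the document.** 14 parameters and four visits (2.5); two-sided 0.05 (2.11.2); 1:1 allocation (2.4.1). The base sample of 39 is split 20 and 19. The between-visit correlation of 0.5 is the repeated-measures value in 2.3.

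**Assumed.** Correlation between parameters is not given. A common value of 0.5 or 0.7 is used, with wider values as a check.

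**Which visits count.** Day 11 is before ascent. The 6-month visit comes after dosing, which ends 7 days after return. Days 17 and 28 are the visits that bear on the two phases in the hypothesis, giving 14 × 2 = 28 tests. All four visits give 14 × 4 = 56.

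**Independent tests,** 1 − 0.95^k:
- k = 14: 51%
- k = 28: 76%
- k = 56: 94%

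For two-sided tests on jointly normal statistics, positive or negative correlation can only lower these values, so they are upper bounds.

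**Correlated tests.** Two-sample t-tests were simulated under no effect, 20 against 19, with between-visit correlation 0.5. The table gives the chance of at least one p below 0.05.

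| Family | Parameter correlation 0.5 | Parameter correlation 0.7 |
|---|---|---|
| One test per parameter (14) | 36% | 25% |
| Days 17 and 28 (28) | 56% | 42% |
| Days 17 and 28, favourable direction only | 29% | 22% |
| All four visits (56) | 77% | 62% |

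The favourable-only row takes every parameter as oriented so that higher is better. Its reference value for a single test is 2.5%, not 5%.

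**Sensitivity.**
- Near-duplicates modelled as clusters (0.9 within, 0.3 across): 52% for two visits.
- Parameter correlation 0.9: 24% for two visits, 40% for four.
- Some parameter significant, in either direction, on both day 17 and day 28: about 7-35%, depending on the correlations and on whether it must be the same parameter.
- The same both-visits rule counting favourable results only: about 4-7%.

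**After the fix.** Peak VO2 tested at two visits with either sufficing and no adjustment would still give up to 1 − 0.95² = 9.75%. Requiring both at 0.05, or using Holm across the two, keeps the rate at or below 5%.

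**The case against.** Five arguments can be made for the plan.

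1. **Direction.** The hypothesis is improvement, while two-sided counts include results against ubiquinol. This stands, and roughly halves the figures. Some parameters have no obvious favourable direction, so the relevant value may lie between the two sets.
2. **Family.** Two of the four visits do not test the hypothesis directly, so 56 tests is a generous count. The model and the sample size both point to the treatment-by-altitude interaction, which could mean one test per parameter, or 14. This also stands, but 25-36% remains several times 5%.
3. **Both phases.** The hypothesis speaks of both phases. If both had to be positive the rate would be much lower, and near 5% on the strictest reading. The document states no such rule, however, so this reading cannot be credited to the plan. Nor does it state that any one parameter at any one visit suffices.
4. **Redundancy.** Near-duplicates lower the effective number of tests. The clustered calculation allows for this and still gives about half. Percent predicted peak VO2 is not a pure restatement of peak VO2 either, since the predicted value differs between people.
5. **Status.** The Discussion calls the results preliminary and in need of confirmation in a large cohort. That tempers the claim, but the article still declares a primary hypothesis, a primary outcome, 90% power and a significance threshold.

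**Conclusion.** The point holds. The primary outcome is a list with no deciding variable and no success rule, and the one adjustment named has no effect here. The chance of a false-positive primary finding on days 17 and 28 is about 42-56%, or about 22-29% counting favourable results only, and about 25-36% with one test per parameter. These figures rest on assumed parameter correlations of 0.5 to 0.7 and a visit correlation of 0.5. Nearly every reading exceeds 5%; the exception is a both-visits, favourable-only rule that the document does not contain.

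A reader might go further and infer that a positive trial is likely even if ubiquinol does nothing, citing 94%. The documents do not support that. The 94% needs 56 independent tests, including two visits outside the hypothesis, and parameters that share components are not independent. On the relevant visits the two-sided range straddles one half and the favourable-only range is well below it. What can be said is that the error rate is uncontrolled and probably several times 5%.

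**What to change.** Amend 2.5 and 2.11.2 by a dated change before unblinding:

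- Name peak VO2, with its unit (ml/min/kg), as the single primary variable. The protocol's own gold-standard label supports this.
- Make the ubiquinol-placebo difference at day 17 and at day 28 the only primary contrasts.
- State the success rule for the two visits. Either both must be significant at two-sided 0.05, which matches the wording of the hypothesis, or either suffices with Holm across the two (smaller p against 0.025, the other against 0.05).
- Move the other 13 parameters, and the day 11 and 6-month visits, to secondary or supportive status with confidence intervals.
- Remove LSD as the stated multiplicity adjustment for the primary claim.

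A fixed order, day 17 then day 28, is also valid but optional. It would bar a day 28 claim if day 17 failed, although the hypothesis gives de-acclimatization equal standing.

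No new data are needed. The cost is that a result on one of the other 13 parameters alone is no longer a primary claim, and that either success rule loses some power. As an illustration, if each visit had 90% power, requiring both would give between 0.9 × 0.9 = 81% (independent visits) and 90% (perfectly correlated). Keeping all 14 parameters primary would cost more: Bonferroni thresholds would be 0.05/14 = 0.0036 with one test each, or 0.05/28 = 0.0018 for two visits.

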## Abstract

Cardiorespiratory function influences exercise capacity and is an important determinant of high-altitude adaptation. Some studies have investigated the characteristics of changes in cardiorespiratory fitness during high-altitude acclimatization. However, studies on changes in cardiorespiratory fitness during high-altitude de-acclimatization are still lacking and have not yet been elucidated. Furthermore, few drugs have been studied to improve cardiorespiratory function during both processes. The Shigatse CARdiorespiratory Fitness (SCARF) study is a single-center, randomized, double-blind, placebo-control clinical trial to explore the effects of ubiquinol on cardiorespiratory fitness during high-altitude acclimatization and de-acclimatization in healthy adults. Participants will be randomly assigned 1:1 to ubiquinol 200 mg daily or a placebo for 14 days before departure until the end of data collection after return in 7 days. Cardiorespiratory fitness is the primary outcome, while acute mountain sickness and high-altitude de-acclimatization symptoms are secondary endpoints. In addition, laboratory measurements, including routine blood tests and serological measurements, will be performed. To the best of our knowledge, the SCARF study will be the first to reveal the changes in the cardiorespiratory fitness characteristics during high-altitude acclimatization and de-acclimatization. Furthermore, the results of this study will contribute to exploring whether ubiquinol supplementation could be beneficial for endurance exercise capacity at different altitudes and help improve adaptation to acute hypoxia and de-acclimatization.

**Clinical Trial Registration:** This study has been registered in the Chinese Clinical Trial Register (www.chictr.org.cn) as ChiCTR2200059900 and ChiCTR2200066328.

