### Recruitment and study population

2.2.

Enrolment occurred in Chongqing (low altitude area, 300 m) from June 1st, 2022, and ended on June 15th, 2022. Demographic and medical data of all participants were recorded through interviews. A potential participant must meet all the inclusion criteria and do not meet any exclusion criteria. The inclusion and exclusion criteria are detailed in Table 2. According to previous studies, the risks associated with CoQ10 are minor, even at doses as high as 1,800 mg (25). Moreover, pharmacokinetic studies suggest that exogenous CoQ10 does not influence the biosynthesis of endogenous CoQ10 and is less likely to accumulate in plasma or tissues after the cessation of supplementation (26).

**Table 2 T2:** Inclusion and exclusion criteria.

Inclusion criteria	Age >18 years
	Chinese Han people
	Have no recent (previous 6 months) experience in resistance exercise (including additional cardiopulmonary exercise tests, long-distance running, riding, swimming and skiing and other endurance exercise)
	Are able to perform leg-based resistance exercise
	Are free from musculoskeletal injury (past 6 months)
	Lived at low altitudes (<500 m) for at least 10 years
	Had no recent exposure to high altitude (>2,500 m) (in the last 6 months)
	Willing and capable of providing written informed consent and complying with the study protocol
Exclusion criteria	Incapable of giving informed consent
	Respiratory and cardiovascular diseases
	Liver and kidney dysfunctions
	Malignant tumors
	Coagulation disorders
	A history of AMS
	History of angioedema
	A history of syncope (hypoglycemia excepted)
	Psychiatric disorders or neuroses
	Ubiquinol supplementation with any side-effect in the first 14 days before departure
	Pregnant or nursing women
	A recent history (previous 1-month period) of drug use with acetaminophen, aspirin, nonsteroidal anti-inflammatory drugs
	A recent history (previous 1-month period) of drug use of acetazolamide, diuretics, or other drugs for the prevention or treatment of AMS
	A recent history (previous 1-month period) use of consuming ergogenic aids (e.g., creatine monohydrate), protein-based supplements, or nutritional supplements that may alleviate muscle damage (e.g., antioxidants, polyphenols)
	Other diseases that prevent the patient from going to high altitudes
	Involuntary participant status

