### Study design

2.6.

Figure 1 shows the flow chart of this study. Participants will take ubiquinol orally with a dose of 200 mg daily or a placebo for 14 days before departure. Physical examination, symptoms related to high-altitude acclimatization and de-acclimatization, cardiorespiratory exercise test, laboratory test, and any possible adverse reaction of ubiquinol and exercise will be collected at baseline detection and each visit. During the 14 days of the medication, only participants who did not experience these adverse effects would go to the high altitude as scheduled. It would help us identify related symptoms at high altitudes due to hypoxia rather than adverse events of ubiquinol. The laboratory and exercise tests will be conducted separately on the last three days of the 14 days. Subsequently, they will board a flight to Shigatse (high altitude area, 3,900 m) in 3 h. After arriving at Shigatse, the AMS symptom self-administered questionnaires and adverse reactions of ubiquinol will be followed up daily, and the other prior programs will be carried out on the third day. The subjects will then be flown back to a low altitude after staying for 7 days at a high altitude and scored for HADAS, followed by other prior programs at a low altitude on the 7th day after return. The last visit will be set in the sixth month of this study, which has not yet been conducted. Laboratory tests include a blood routine test of 19 parameters commonly used in the clinic and a serological test of 19 circulating indicators, including glucose, total cholesterol, triglyceride, low-density lipoprotein cholesterol, high-density lipoprotein cholesterol, lactate, non-esterified fatty acid, norepinephrine, epinephrine, plasma renin activity, angiotensin Ⅱ, angiotensin-converting enzyme 2, neuropeptide Y, atrial natriuretic peptide, lactate dehydrogenase, insulin, glucocorticoid, adiponectin, and leptin.

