Cardiorespiratory fitness reflects the comprehensive ability of the body to transport and utilize oxygen and embodies the overall function of the respiratory and cardiovascular systems (49, 50). VO_2_max is the gold standard for assessing cardiorespiratory fitness and an independent predictor of cardiovascular events and mortality (51–53). Previous studies have indicated that VO_2_max decreases linearly by approximately 8% for every 1,000 m of additional elevation above 700 m, while it descends in an accelerated curve over 6,300 m, suggesting that cardiorespiratory function is impaired at high altitudes (54). However, there is limited information on cardiorespiratory fitness changes during de-acclimatization from a high altitude in healthy individuals, and the underlying mechanisms remain to be elucidated. Thus, in this study, we try to illuminate the possible mechanism by circulating markers of metabolism and the autonomic nervous system (55).

This study has some limitations. First, although this is not a small clinical trial in the CPET trial at a high altitude, this study is limited by a small sample size (*n* = 41) and short follow-up (on days 17 and 28, respectively). Therefore, it is troublesome to implement hierarchical analysis, and these preliminary results need to be confirmed in a large cohort. Second, long-term follow-up may be more meaningful in evaluating ubiquinol supplements on cardiorespiratory fitness.

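### The primary CPET outcome includes a 6-month test about five months after dosing ends, and the stated model, read literally, pools that test with the other low-altitude visits

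*Protocol article*

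**What the plan says.** Section 2.5 gives the scope of the primary outcome as "cardiorespiratory fitness characteristics both at high-altitude acclimatization and de-acclimatization after ubiquinol supplementation". It then lists 14 CPET parameters whose values "at these four visits will be collected for further analysis". The visits are identified elsewhere. Section 2.4.1 states "Clinical follow-up will be scheduled on days 11, 17, 28, and 6 months after the study began", and Table 1 marks CPET at all four. Section 2.6 adds: "The last visit will be set in the sixth month of this study, which has not yet been conducted".

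Two other places describe a shorter trial. The Abstract sets dosing "for 14 days before departure until the end of data collection after return in 7 days". The limitations paragraph of the Discussion refers to "short follow-up (on days 17 and 28, respectively"), and then remarks that longer follow-up might be more informative.

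Section 2.11.2 specifies generalized estimating equations (GEE) with an exchangeable working correlation. The terms are treatment, altitude and treatment by altitude, with a comparison of the two groups at each altitude. No visit or time term is named, and the levels of altitude are not defined. The document mentions two test sites: Chongqing at 300 m (section 2.2) and Shigatse at 3,900 m (section 2.6).

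**The concern.** The hypothesis concerns fitness during the stay at altitude and during the return phase, under supplementation. Day 17 tests the first and day 28 the second. At 6 months participants have been back at low altitude for months and are long off treatment, yet that test belongs to the primary outcome on the same footing as the others.

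The analysis factor is altitude, not visit. If altitude has two levels, days 11 and 28 and month 6 share the low level, and the low-altitude comparison between groups is an average over all three. That comparison carries the de-acclimatization half of the primary hypothesis. If the effect has gone by 6 months, a real benefit on return is pulled toward null. Whether this happens depends on a coding choice that the text leaves open, and the text also disagrees about whether the visit is part of the trial's follow-up.

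**Working it through.** **Timing.** From the Abstract and section 2.6, dosing ends at about day 14 + 7 + 7 = 28. Six months is day 168 (24 weeks) to day 183. The gap is 168 − 28 = 140 to 183 − 28 = 155 days, or 4.6 to 5.1 months at 30.44 days per month. Section 2.6 by itself states only the 14 pre-departure days of intake; on that reading the gap is 14 days longer.

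**The plan's own sample size.** Inputs from section 2.3: two groups, α 0.05, power 0.9, correlation ρ = 0.5, ε = 1, N = 39 inflated for 5% dropout, and N = 36 for the within-between interaction.
- Inflation: 39 × 1.05 = 40.95, which gives the stated 41.
- Interaction: the effect size f and the number of measurements m are not stated. With f = 0.25 assumed and m = 3, λ = f²Nm/(1 − ρ) = 0.0625 × 36 × 3 / 0.5 = 13.5 on 2 and 68 degrees of freedom, and power is 0.906. N = 36 is then reproduced exactly. With m = 4 the same f needs only N = 30.

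The stated 36 therefore fits three measurements rather than four, but only under an assumed f.

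**Effect of pooling at low altitude.** Under equal correlation ρ, the mean of k visits has variance (1 + (k − 1)ρ)/k in units of the single-visit variance. At ρ = 0.5 this is 0.750 for k = 2 and 0.667 for k = 3. Take an effect of 1 at days 11 and 28 and 0 at 6 months.

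| Low-altitude visits pooled | Mean effect | Relative noncentrality |
|---|---|---|
| Days 11, 28 | 1 | 1²/0.750 = 1.33 |
| Days 11, 28, month 6 | 2/3 | (2/3)²/0.667 = 0.67 |

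The noncentrality halves. For a two-sided 5% test with 90% power, 1.960 + 1.282 = 3.242. After pooling it is 3.242 × √0.5 = 2.292, and power is Φ(2.292 − 1.960) = Φ(0.332) = 0.63. The F-test version at N = 39 gives the same 63%.

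**Simulation.** A 300-run GEE simulation with exchangeable correlation used 20 per arm, 0.80 SD at days 11, 17 and 28, and 0 at 6 months.
- Two-level altitude: the low-altitude estimate falls from 0.80 to 0.54 SD when the 6-month test is added. The high-altitude estimate stays at 0.80.
- Each visit its own level: the estimates at days 11, 17 and 28 are 0.80 with or without the 6-month test.

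**Range for the assumption.** Let a fraction p of the effect persist at 6 months. The pooled effect is (2 + p)/3, and the noncentrality ratio is ((2 + p)/3)²/0.667 ÷ 1.33.

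| p | Pooled effect | Noncentrality ratio | Power (from 90%) |
|---|---|---|---|
| 0 | 0.67 | 0.50 | 63% |
| 0.5 | 0.83 | 0.78 | 82% |
| 1 | 1.00 | 1.13 | 93% |

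The loss depends on how much effect remains, and with full persistence it becomes a small gain.

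**The case against.** The strongest reply is that no single effect averaged over four visits is planned. Section 2.11.2 includes an interaction and compares groups at each altitude. That stands, and it limits the point in three ways: the high-altitude contrast is untouched under separate-visit or two-level coding; separate visit levels lose nothing; and a null fourth visit can help the interaction test (for effects 0, 1, 1 at days 11, 17 and 28, relative noncentrality rises from 1.33 to 2.00).

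A reader might infer that the whole treatment effect is diluted. An average over all visits would indeed fall to 3/4 of its value, with noncentrality going from 1/0.667 = 1.5 to 0.75²/0.625 = 0.9 and power from 90% to about 71%, but the protocol does not name that average as its test. A comparison of days 17 and 28 with all four visits gives about 43% (3.242 × 0.5/√(0.625/0.75) = 1.78). That figure also assumes no effect at day 11 and charges its loss to the 6-month visit: adding a null day 11 alone already gives 3.242 × (2/3)/√(0.667/0.75) = 2.29, or 63%.

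A reader might also take section 2.2 to say that nothing is left to find at 6 months. Its statement that exogenous CoQ10 "is less likely to accumulate in plasma or tissues after the cessation of supplementation" is about accumulation and follows a sentence on safety. It gives no washout time and no duration of effect on fitness.

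Table 1 schedules the de-acclimatization symptom assessment at 6 months, so the protocol evidently sees the visit as long-term follow-up, which is legitimate. The limitations text may describe follow-up to date, since the 6-month visit had not yet taken place. And the Abstract's phrase "until the end of data collection after return in 7 days" sits in a sentence about dosing. These readings soften the inconsistency but do not settle which visits make up the primary data. Nor do they define the altitude levels. There is also no basis for saying that the 6-month visit will have the most missing data: the only attrition figure is 5% overall.

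**Conclusion.** The concern holds in a limited form. An off-treatment visit outside the stated hypothesis is part of the primary outcome, the document is inconsistent about it, and the stated model permits it to be pooled with the other low-altitude visits. Under two-level altitude coding, an equal effect at days 11 and 28, none at 6 months, and ρ = 0.5, the low-altitude effect falls by one third and 90% power falls to about 63%. The absence of an effect at 6 months is an assumption, not something the protocol states. Dilution is a consequence of the literal model, not a certainty: the acclimatization contrast at day 17 is safe, and so is everything else if visits are kept separate. The point should be settled in the protocol because it fixes what the de-acclimatization comparison estimates.

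**What to change.** - In section 2.5, name day 17 (acclimatization) and day 28 (de-acclimatization) as the primary time points, with day 11 as the pre-ascent visit.
- In section 2.11.2, use visit instead of altitude as the repeated factor, so that low-altitude visits are not pooled. This also separates day 28 from day 11, which a two-level altitude factor would merge even without the 6-month test.
- Analyse the 6-month CPET separately as exploratory off-treatment follow-up, outside the primary treatment and interaction terms.
- Align the Abstract, Table 1, section 2.5 and the Discussion on which visits are primary and when follow-up ends.

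These are changes of wording and model specification. The 6-month visit can still be held. The downside is that it no longer contributes to the primary claim.
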